# Morita therapy for depression and anxiety (Morita Trial): study protocol for a pilot randomised controlled trial

**DOI:** 10.1186/s13063-016-1279-3

**Published:** 2016-03-24

**Keywords:** Morita therapy, Major depressive disorder, Mixed methods, Feasibility study

## Abstract

**Background:**

Morita Therapy, a psychological therapy for common mental health problems, is in sharp contrast to established western psychotherapeutic approaches in teaching that undesired symptoms are natural features of human emotion rather than something to control or eliminate. The approach is widely practiced in Japan, but untested and little known in the UK. A clinical trial of Morita Therapy is required to establish the effectiveness of Morita Therapy for a UK population. However, a number of methodological, procedural and clinical uncertainties associated with such a trial first require addressing.

**Methods/Design:**

The Morita Trial is a mixed methods study addressing the uncertainties associated with an evaluation of Morita Therapy compared with treatment as usual for depression and anxiety. We will undertake a pilot randomised controlled trial with embedded qualitative study. Sixty participants with major depressive disorder, with or without anxiety disorders, will be recruited predominantly from General Practice record searches and randomised to receive Morita Therapy plus treatment as usual or treatment as usual alone. Morita Therapy will be delivered by accredited psychological therapists. We will collect quantitative data on depressive symptoms, general anxiety, attitudes and quality of life at baseline and four month follow-up to inform future sample size calculations; and rates of recruitment, retention and treatment adherence to assess feasibility. We will undertake qualitative interviews in parallel with the trial, to explore people’s views of Morita Therapy. We will conduct separate and integrated analyses on the quantitative and qualitative data.

**Discussion:**

The outcomes of this study will prepare the ground for the design and conduct of a fully-powered evaluation of Morita Therapy plus treatment as usual versus treatment as usual alone, or inform a conclusion that such a trial is not feasible and/or appropriate. We will obtain a more comprehensive understanding of these issues than would be possible from either a quantitative or qualitative approach alone.

**Trial registration:**

Current Controlled Trials ISRCTN17544090 registered on 23 July 2015.

**Electronic supplementary material:**

The online version of this article (doi:10.1186/s13063-016-1279-3) contains supplementary material, which is available to authorized users.

## Background

Clinical depression and generalised anxiety disorder are the two most common mental health disorders [1], with one in six people in the UK experiencing such a disorder each year [2]. Together, depression and anxiety are estimated to cost the UK economy £17bn in lost output and direct health care costs annually, with a £9bn impact on the Exchequer through benefit payments and lost tax receipts [3].

**Table 1 Tab1:** World Health Organization Trial Registration Data Set

Data category	Information
Primary registry and trial identifying number	Current Controlled Trials database
	ISRCTN17544090
Date of registration in primary registry	23-Jul-15
Secondary identifying numbers	N/A
Source(s) of monetary or material support	University of Exeter Medical School, UK
Primary sponsor	University of Exeter, UK
Secondary sponsor(s)	N/A
Contact for public queries	[name]
	University of Exeter Medical School, UK
	[contact]
Contact for scientific queries	[name]
	University of Exeter Medical School, UK
	[contact]
Public title	The Morita Trial
Scientific title	Morita Therapy for Depression and Anxiety: A Feasibility and Pilot Study
Countries of recruitment	UK
Health condition(s) or problem(s) studied	Depression
Intervention(s)	Morita Therapy
	Treatment as usual
Key inclusion and exclusion criteria	Ages eligible for study: ≥18 years;
	Sexes eligible for study: both;
	Accepts healthy volunteers: no
	Inclusion criteria: adult patient (≥18 years), current DSM Major Depressive Disorder
	Exclusion criteria: cognitive impairment, bipolar disorder or psychosis/psychotic symptoms, substance dependence, acute suicidal risk, current psychological therapy
Study type	Interventional
	Allocation: randomised intervention model
	Primary purpose: treatment
	Phase II
Date of first enrolment	Sep-15
Target sample size	72
Recruitment status	Recruiting
Primary outcome(s)	Depressive symptoms, generalised anxiety symptoms, quality of life, attitudes (at four-month follow-up); qualitative exploration of acceptability.
Key secondary outcomes	N/A

**Fig. 1 Fig1:**
[figure not shown]
Consolidated Standards of Reporting Trials (CONSORT) diagram describing flow of participants through the study

**Fig. 2 Fig2:**
[figure not shown]
Schematic diagram describing timeline for participants in the study

Depression accounts for the greatest burden of disease among all mental health problems, and is the second-highest among all general health problems [4]. The lifetime prevalence of depression has been estimated at 16.2 %, and rates of co-morbidity and risk for suicide are high [5–7]. Depression is also recurrent, with over three quarters of people who recover from one episode experiencing at least one more [8].

Generalised Anxiety Disorder (GAD) affects between 2–5 % of the UK population at any one time, and accounts for up to 30 % of the mental health problems presented to General Practitioners (GPs) [2]. The lifetime prevalence of GAD has been estimated at 5.7 % [9]. Furthermore, the comorbidity between anxiety and depression make a strong contribution to the total disability attributed to mental disorders [1].

Medication and Cognitive Behavioural Therapy have the strongest evidence-base for treating these conditions, and are each recommended by the National Institute for Health and Care Excellence (NICE) [10, 11]. However, many patients are refractory to such interventions [12], with both depression and anxiety remaining chronic disorders despite treatment [1]. Recovery is only reached by 55–56 % of people receiving treatment through the large-scale UK initiative to provide NICE recommended psychological therapies (‘Improving Access to Psychological Therapies’ (IAPT)) [13, 14], thereby increasing the risk of future relapse and the maintenance of recurring and chronic problems [15].

Thus, it is important to develop and test new potentially effective treatments for depression and anxiety in order to treat a wider range of patients [15] and provide patients in the UK with choice alternatives.

### Morita Therapy

Morita Therapy is a psychotherapy developed in Japan by [name] in 1919 [16] used for the treatment of common mental health problems. Morita Therapy was originally developed in inpatient settings for patients with particular psychological problems, including but not limited to GAD [17]. More recently, Morita Therapy has been applied to a wider range of conditions, including depression, and guidelines for practicing outpatient Morita Therapy have been developed [17]. Morita Therapy is now widely practiced in Japan, and has branches in various other countries including North America, Australia, China, Russia and Rwanda [18].

Morita Therapy is a holistic approach, aiming to improve functioning in everyday life, rather than an approach targeting specific symptoms [18]. The underlying premise is that unpleasant symptoms are part of the natural ecology of the human experience. Morita Therapy thus helps patients to re-orientate themselves in the natural world and takes a restorative approach to potentiate their natural healing capacity. Morita therapists help patients to move away from symptom preoccupation and combat, which it is conceptualised both interfere with this natural recovery process and lead to preoccupation with and worsening of symptoms [17]. By helping patients to accept that undesired symptoms are natural features of human emotion rather than something to control or eliminate, and that emotions ebb and flow as a matter of course and can be lived with, Morita Therapy is in sharp contrast to established western psychotherapeutic approaches with their focus on symptom elimination. In Morita Therapy, patients are taught to live with, rather than be without, unpleasant emotions.

### Uncertainties: The need for a mixed methods feasibility study

As with the development of many other treatments to date [15], initial evidence for Morita Therapy’s efficacy is largely based on case studies, predominantly conducted in Japan. A narrative review of forty-nine such studies and four quasi-experimental studies indicated that Morita Therapy has been reported as effective for a diverse range of issues, but that further work is required to both standardise its delivery and investigate its efficacy in controlled trials (personal communications: [name]).

Furthermore, Morita Therapy is currently little known in the UK. Thus, evidence of the efficacy of Morita Therapy based on truly experimental studies, and evidence of the effectiveness of Morita Therapy specifically for a UK population, has not yet been established. Whilst a fully-powered UK randomised controlled trial (RCT) of Morita Therapy versus treatment as usual is needed to establish the effects of Morita Therapy, a number of clinical, procedural and methodological uncertainties currently prevent us moving immediately to such a trial.

With respect to clinical uncertainties, the operationalisability of the UK Morita Therapy outpatient protocol, and the acceptability of both the protocol specifically and Morita Therapy in general, is unknown. Gathering data on these uncertainties is essential to ensure that the treatment administered in a large-scale trial is deliverable by therapists, and acceptable to both therapists and patients.

With respect to procedural uncertainties, information is required on the likely rates of recruitment to and retention in a trial of Morita Therapy, and of treatment adherence, in order to assess the feasibility of a trial and inform the required sample size. With respect to methodological uncertainties, estimates of the variance in participant outcomes and information on how these correlate with baseline scores are also required to inform future sample size calculations.

In line with the Medical Research Council (MRC) framework for the development and evaluation of complex interventions [19], all such uncertainties are appropriate to address within a pilot trial and feasibility study [20]. In order to both collect the required quantitative data and understand people’s views of Morita Therapy, qualitative work will be embedded in a pilot randomised controlled trial of Morita Therapy compared to treatment as usual, and merged with quantitative data on treatment adherence to potentially help explain variability in participants’ therapeutic engagement.

### Study purpose

The purpose of this study is to prepare the ground for the design and conduct of a fully-powered RCT of Morita Therapy plus treatment as usual versus treatment as usual alone, or to conclude that such a trial is not appropriate and/or feasible.

### Research questions

What proportion of participants approached to take part in the trial will agree to do so?What proportion of participants who agree to take part in the trial will remain in the trial at four month follow-up?What proportion of participants who agree to take part in Morita Therapy will adhere to a pre-defined per-protocol dose of Morita Therapy?What is the variance in participant outcomes following Morita Therapy plus treatment as usual and treatment as usual alone, and how do they correlate with participants’ baseline scores?What are the estimated between-group differences (and 95 % confidence intervals) in participant outcomes following Morita Therapy plus treatment as usual and treatment as usual alone?How acceptable is Morita Therapy to participants and therapists?How do participants’ views about Morita Therapy relate to the variability in the number of treatment sessions they attend?

### Criteria for success

The criteria to be met in order to deem a fully-powered RCT feasible as is [20] are:A sufficient number of participants to populate a fully-powered trial are likely to be recruited and retained, i.e. we recruit at the rate anticipated in the pilot trial (12 % of those invited) and experience an attrition rate no higher than 20 % of those randomised, in line with our other National Institute of Health Research (NIHR) mental health trials [21–23]. We will consider whether protocol modification or close monitoring during a fully-powered RCT will address any failure to meet these criteria [20].The levels of engagement with and adherence to Morita Therapy are likely to be on par with our other NIHR mental health trials [23], i.e. at least 65 % of patients allocated to Morita Therapy attend at least 40 % of treatment sessions. Any failure to meet this criterion will be considered in the light of participants’ views on the acceptability of Morita Therapy in order to determine whether protocol modification or close monitoring are sufficient to deem a fully-powered RCT feasible [20].It is likely that a Morita Therapy outpatient protocol can be produced which is acceptable to patients and therapists, and deliverable by therapists, as defined by responses to qualitative interviewing.

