### Pilot Randomised Controlled Trial

#### Sample size

A conventional power calculation is inappropriate for the purpose of a pilot trial [20]. Instead, we have calculated the sample size in order to provide useful information about the aspects of the study being assessed for feasibility [20]. Thus, we have constructed confidence intervals based on certain criteria for success [20], specifically: recruiting at a rate of 12 % of those invited and experiencing an attrition rate no higher than 20 % of those randomised. We expect to invite a total of 570 participants to participate in the trial. Thus, we expect to recruit 72 participants into the trial, and follow-up 60 participants (30 in each trial arm).

Inviting 570 participants is sufficient to estimate a participation rate (as percentage of subjects invited) of 10 % with a margin of error of +/− 2.46 %, or to estimate a participation rate of 12 % with a margin of error of +/− 2.67 %, or to estimate a participation rate of 15 % with a margin of error of +/− 2.93 %, based on 95 % confidence intervals. Recruiting 72 participants is sufficient to estimate a follow-up rate (as percentage of participants randomised) of 80 % with a margin of error of +/− 9.24 %, or to estimate a follow-up rate of 85 % with a margin of error of +/− 8.25 %, based on 95 % confidence intervals.

In addition, we will calculate the standard deviation of participant outcomes and the correlation between baseline and four month follow-up scores, which can be used to refine future sample size calculations to incorporate the additional precision obtained from adjusting for baseline scores when comparing outcome scores between the trial arms. 30 participants in each group is sufficient to estimate: (i) the standard deviation of continuous outcomes to within 22 % of their true value based on the upper limit of the 95 % confidence interval; (ii) a Pearson’s correlation coefficient between baseline and follow-up scores with a margin of error of +/− 0.1 if the true correlation is 0.8, or with a margin of error of +/− .14 if the true correlation is 0.7, or with a margin of error of +/− 0.17 if the true correlation is 0.6.

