#### Participant identification and recruitment

Our main method of recruitment will be through searches of General Practice records, conducted by Practice staff. We will recruit six GP Practices in Devon. All GP Practices who are able to access the University of Exeter’s Mood Disorders Centre (MDC) Accessing Evidence-Based Psychological Therapies (AccEPT) Clinic (those within the National Health Service Northern, Eastern and Western Devon Clinical Commissioning Group) will be eligible.

Practice record searches will be limited to patients aged 18 or over and seen within the past three months for depression. The resulting patient names will be screened by the GP with whom the patient is registered for any patients known to meet exclusion criteria or for whom the GP considers the trial unsuitable. The remaining patients will be sent invitations to participate in the trial by Practice staff.

We will also place adverts on websites of the University of Exeter Medical School and AccEPT Clinic, place leaflets in the waiting rooms of consenting Devon General Practices and circulate an email invitation to former MDC participants who have consented to such contact. All invitations and adverts will include a study summary sheet [see Additional file 1] and permission to contact form [see Additional file 2] (Figs. 1 and 2).

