#### Forecast execution dates

The preparatory period started in October 2014. Recruitment is running from September 2015 for approximately ten months. Follow-up and qualitative data will be collected from January 2016 to November 2016. Data analysis and reporting are expected to take another nine months. The total duration of the study will be 24 months.

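### The recruitment success criterion is a bare percentage of those invited, so it can be met with far fewer than 72 recruits in the planned ten months

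*Protocol article*

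**What the plan says.** The first criterion in Criteria for success states the aim as a matter of numbers: "A sufficient number of participants to populate a fully-powered trial are likely to be recruited and retained". It then defines what will count as showing this: "we recruit at the rate anticipated in the pilot trial (12 % of those invited"), and that the trial will "experience an attrition rate no higher than 20 % of those randomised". A missed criterion leads to consideration of protocol modification or of close monitoring in the full trial.

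The first of the Research questions takes the same form: "What proportion of participants approached to take part in the trial will agree to do so". Quantitative analysis likewise reports participant flow as percentages of those invited and of the preceding step, with margins of error.

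Volume and time appear only as plans. Sample size says "We expect to invite a total of 570 participants to participate in the trial" and "Thus, we expect to recruit 72 participants into the trial, and follow-up 60 participants (30 in each trial arm"). Forecast execution dates says "Recruitment is running from September 2015 for approximately ten months". Participant identification and recruitment names six general practices as the main source and adds website adverts, waiting-room leaflets and emails to former participants. Before any practice invitation is sent, each patient's GP removes names from the search list, either because an exclusion is already known or because the GP judges that the study does not suit the patient.

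**The concern.** Whether a full trial can be filled depends on how many people can be reached, what share of them join, and how fast. The criterion measures only the share. It takes the same value whether 570 people or 200 were invited, and whether recruitment took ten months or much longer.

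The number invited is not under the trial's full control. Practice searches cover only patients seen for depression in the previous three months, and GPs remove names before anyone counts as invited. The documents give no figure for how many names survive that step beyond the expected total of 570.

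At stake is the pilot's main verdict. Followed as written, the rule could declare the recruitment side of a full trial feasible without change after a pilot that fell well short of its own target.

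**Working it through.** **Inputs.** Criterion: 12 % of those invited (Criteria for success). Expected invitations 570 and recruits 72 (Sample size). Recruitment window about 10 months (Forecast execution dates). Any invitation count other than 570 is an assumption, used to show how the rule behaves.

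**The plan's own precision.** Margin = 1.96 × √(p(1 − p)/n). With p = 0.12 and n = 570: 1.96 × √(0.12 × 0.88/570) = 2.67 percentage points, which matches Sample size.

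**The plan's own throughput.** 72/10 = 7.2 recruits a month.

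**Number recruited when the criterion is exactly met.** Recruits = 0.12 × invited; pace = recruits/10; months to reach 72 = 72/pace.

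| Invited | Recruits at 12 % | Share of 72 | Per month | Months to 72 at that pace | 95 % margin (points) |
|---|---|---|---|---|---|
| 570 (plan) | 68.4 | 95 % | 6.84 | 10.5 | ±2.67 |
| 400 (assumed) | 48 | 67 % | 4.8 | 15 | ±3.18 |
| 300 (assumed) | 36 | 50 % | 3.6 | 20 | ±3.68 |
| 200 (assumed) | 24 | 33 % | 2.4 | 30 | ±4.50 |

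Every row meets the criterion. The lower rows also estimate the 12 % less precisely than planned.

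**Consistency of 12 %, 570 and 72.** 0.12 × 570 = 68.4, not 72. Reaching 72 from 570 invitations needs 72/570 = 12.6 %; reaching 72 at 12 % needs 72/0.12 = 600 invitations. Recruits from adverts or leaflets could close the gap, but they have no countable number invited. Placing them in the numerator of the 12 % would raise the percentage without any change in response to invitation.

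**What pace means for a full trial.** The article gives no size for the full trial. For an assumed 300 to 500 participants at the pilot's scale, 7.2 a month takes 300/7.2 = 42 to 500/7.2 = 69 months; 3.6 a month takes 83 to 139 months. Both paces are compatible with a 12 % participation rate.

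**The case against.** The strongest reply is that the proportion is a deliberate choice. It is what the first research question asks and what the sample size was built to estimate. Willingness to take part is the unknown that a pilot must measure, while practices, mailing volume and duration can be scaled up later. The target of 72 and the time window are stated, and participant flow will be reported step by step, so a pilot with 36 recruits would visibly miss its plan. Nothing in the documents suggests that GP screening would cut invitations to 300.

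Most of this stands. The proportion belongs in the criterion, and low invitation volume is only a possibility. But a visible shortfall does not fail the criterion, because neither the number nor the window is part of it. Scaling up also requires knowing how many people each source yields and how fast.

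Two stronger readings are not supported. A reader might infer that the pilot would wrongly be declared a failure if a larger mailing with a lower response still reached 72 (for example, an assumed 800 invited at 9 %). The section does not make a missed 12 % decisive; it calls for consideration of modification or monitoring. A reader might also divide 72 and 570 by six and treat 12 recruits or 95 invitations per practice as planned yields. The article makes no such plan: practice searches are the main route, not the only one.

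**Conclusion.** The concern holds as a gap in one direction. The criterion equates a claim about sufficient numbers with a ratio that contains neither number nor time, so it can be passed by a pilot that recruits far too slowly. At an assumed 300 invitations the pass comes with 36 recruits, half the target and half the planned monthly pace; at an assumed 200 it comes with 24. These volumes illustrate what the wording allows and are not predictions. The review clause in the same section is triggered by failure to meet a criterion, so it gives no protection against a false pass. Separately, and using only the plan's own figures, exactly 12 % of 570 gives 68 recruits and not 72. This is a cheap improvement to the pilot's decision rule and does not invalidate the design.

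**What to change.** - Keep the 12 %, and state that numerator and denominator are restricted to people who were individually invited.
- Add to the first criterion that about 72 participants are randomised, by all recruitment routes together, within the planned window of approximately ten months (about 7 a month). Send a shortfall to the same consideration of protocol modification or monitoring that already applies to a missed criterion.
- Set no quota per practice. Report invitations and recruits by practice, month and route, and use that throughput together with the percentage to project a full trial.
- State that 12 % of 570 is 68, so that 72 from 570 invitations needs 12.6 %, or 600 invitations at 12 %, unless other routes contribute.

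The cost is the rewording of one criterion and slightly more reporting, largely from participant-flow data that the trial already collects. The downside is a second condition that the pilot could miss; because a miss leads to review, it would not by itself rule out a full trial.
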